**Figure 2 F2:**
[figure not shown]
Patients general satisfaction to the treatment.

Dosage of thalidomide in patients of integrative group will be recorded. This will to evaluate when combination application with GDPSF, if dosage of thalidomide dosage could be decreased.

Quality of life for BD: The quality of life BD, developed by Gill Gilworth et al, provides us with a simple, reliable, and valid tool for assessing the influence of interventions for BD and for evaluating models of service delivery.^[15]^ It is well accepted by patients and has scaling and psychometric properties.

## Safety assessment

4

Based on current knowledge, GDPSF has rarely side effects, and unlikely cause adverse events (AEs). Anyway, uncomfortable react after taking will be recorded. Potential AEs caused by thalidomide in adults include neutropenia, leukopenia, lymphopenia, anemia, thrombocytopenia, peripheral neuropathy, confusion, depressed mood, reduced coordination, tremor, dizziness, tingling, numbness, constipation, peripheral edema, liver damage, menopause, heart failure, difficulty breathing, interstitial lung disease, lung inflammation, vomiting, dry mouth, rashes, dry skin, fever, weakness, and a sense of unwellness.^[16]^

The contact information of the experimenters will be informed to every subject. If there are any AEs, participants can inform the investigator anytime. Appropriate treatment to the AEs occurred will be provided. In case of serious AEs, the subject shall stop the medicine, and been recommended to other treatment options. All of the AEs in 3 groups will be recorded for assessment.

### Statistical considerations

4.1

#### Sample size calculation

4.1.1

One of the aim in the study aims to detect the symptoms easing effect of GDPSF in BD through historical control. The complete remission of symptoms rate reported ranged from 22% to 81%, while effective rate generally above 70%.^[17]^ The reported complete remission rate of thalidomide for BD symptoms ranges from 6% to 81%.^[18,19]^ We also interested in the effects of GDPSF or its combination application with thalidomide compared with thalidomide alone, especially on whether GDPSF improved outcomes or reduce thalidomide intake and its side effects.

Since no strict randomized controlled trials have been previously performed, we proposed this study to evaluate the feasibility of a large-scale clinical trial. Anticipating a 20% dropout rate, a total of 150 patients, with 50 patients in each group, will be recruited for this pilot study.

### Statistical analysis

4.2

This is an 18 months clinical trial, in which participants will receive treatment for 6 months and accept a 12 months follow-up. During their treatment, participants will visit investigators every 4 weeks 5 times in all. Their clinical manifestations (MAI), blood tests, thalidomide dosage in thalidomide, and integrative groups will be assessed. Participants will receive 2 times of follow-up for 12 months after treatment, their remission levels, quality of life, and satisfactory levels will be assessed. Figure 3 summarizes the study schedule of enrollment, interventions, and assessments according to the SPIRIT 2013 statement. The data of assessments on each intervention group before and after treatments will be collected and analyzed through historical control, while between groups through intergroup control method.

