### Objective

2.1

The primary objective of this study is to ascertain the potential curative or improvement effects and safety of GDPSF for BD patients with mucocutaneous involvement only. The secondary objective is to determine whether combination application of GDPSF and thalidomide could possibly reduce the side effects caused by thalidomide and increase effectiveness for BD management.

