## Discussion

5

In this pilot study, we chose mucocutaneous type of BD patients as out eligible patients, because, if the disease involved vital organs already, intensive treatments will be needed, which makes the simple application of GDPSF or thalidomide not safe for patients. The symptoms caused by the disease especially recurrent oral and genital ulceration cause pain and decrease quality of life in BD patients, lead them suffer physically and psychologically.^[20]^ As a result, it is not proper to give a BD patient placebo treatment as a control. Thalidomide is one of the most common options to erase symptoms in adult BD patients. It provided a useful therapeutic option in severe oral and genital ulceration, which had not responded to other therapies.^[20]^ Therefore, besides of historical control, thalidomide treatment group will set as a control.

Traditional Chinese medicine (TCM) gained afflatus from war that similar principles dominate in both military and medicine, which is to prescribe drugs as monarch, minister, assistant, and guide in a formula according to military action strategies or country governance. In the formula of GDPSF, the *G uralensis* plays the role of monarch, which targets the disease or main symptoms suffered. There has been numerous of in vivo and in vitro researches on antiinflammatory activity from *G uralensis*.^[21,22]^ Extracts from *S baicalensis* also showed activity of antiinflammation, antitumor, and attenuates oxidant stress.^[23,24]^ Researches on *P ternate* shows antidepression, gastrointestinal regulation,^[25,26]^ and effects on blood pressure.^[27]^*C chinensis* shows activity of antimicrobial,^[28]^ while mycobacterial such as *Streptococcus* were though as one of the risks to induce the onset of oral ulcers in BD.^[29]^ The multiple functions of *S baicalensis*, *C chinensis*, and *P ternate* can be used to assistant monarch to enhance the effectiveness for the main disease or symptoms, play a role of minister. Potential side effects in the formula based on TCM would relieve by *P ginseng*, which has been richly investigated. As the chemical elements are extremely complex in n herb formula, and considering the relation between parts and whole, it is impossible to illustrate the GDPSF pharmaceutical actions through current researches on extractives. Good news is the compound formula is gaining attention.^[30]^

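### GDPSF's symptom effect is assigned to a before-after comparison mislabelled historical control, and the randomised comparison with thalidomide is planned but not made decisive

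*Protocol article*

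**What the plan says.** Section 2.1 (Objective) names no comparator: "The primary objective of this study is to ascertain the potential curative or improvement effects and safety of GDPSF for BD patients with mucocutaneous involvement". Section 4.1.1 (Sample size calculation) then gives the route to that effect: "One of the aim in the study aims to detect the symptoms easing effect of GDPSF in BD through historical control". Section 4.2 (Statistical analysis) applies the same term to each arm's own data: "The data of assessments on each intervention group before and after treatments will be collected and analyzed through historical control". The Methods part of the abstract says the same.

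The randomised comparison is also in the plan. Section 4.2 continues: "while between groups through intergroup control method". Section 2.2 (Study design) intends to compare remission and ineffective rates across the treatment groups, and section 4.1.1 states an additional interest in GDPSF, alone or combined, against thalidomide alone. The Discussion (section 5) sets out the relation between the two: "Therefore, besides of historical control, thalidomide treatment group will set as a control".

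Section 4.1.1 also cites published complete remission rates: 22% to 81% with no treatment named, and 6% to 81% for thalidomide. It calls the trial a pilot of 150 patients, 50 per group, with 20% dropout expected.

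**The concern.** A historical control is an external group observed earlier. What section 4.2 describes is a change from each patient's own baseline. That change adds together any drug effect, the natural relapse-and-remit course, and regression to the mean in patients who enter while their disease is active. The protocol itself calls the ulceration recurrent (section 5) and grades response partly by relapse frequency and by a fall in the mucocutaneous activity index (section 3.1). No arm receives placebo alone, so the within-group data contain nothing that separates these components.

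At stake is which result answers the primary objective. With every test at P < .05 and no ranking of the two analyses, a significant before-after change in the GDPSF arm could be reported as the finding, although an inert preparation could produce the same change. The randomised thalidomide arm, which shares the same drift, would then not bear on the conclusion.

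**Working it through.** **The plan's own figure.** 3 × 50 = 150, and 50 × (1 − 0.20) = 40 completers per group. No effect size, power, margin or benchmark rate is stated, so nothing further can be reproduced. The figure of 40 is used below.

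**Published rates as a benchmark.** The first range is 81 − 22 = 59 points wide and the thalidomide range is 81 − 6 = 75 points. An exact one-sided 0.05 test with 40 patients would need at least 14 responders (35%) against 22%, but at least 37 (92.5%) against 81%. The verdict therefore depends on which value is chosen, and the protocol chooses none.

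**Before-after change with no drug effect.** Assumptions, none taken from the protocol except n = 40: standard normal score in the patient population, entry only above the median, correlation ρ between baseline and follow-up, paired t test at two-sided 0.05.

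- Mean baseline above the median = √(2/π) = 0.798 SD; variance of that baseline = 1 − 2/π = 0.363.
- Expected fall = (1 − ρ) × 0.798.
- Variance of the fall = (1 − ρ)² × 0.363 + (1 − ρ²).
- Noncentrality = √40 × (expected fall / SD of the fall).

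| ρ | Expected fall (SD) | SD of fall | Noncentrality | Trials declaring improvement |
|---|---|---|---|---|
| 0.3 | 0.559 | 1.043 | 3.39 | about 91% |
| 0.5 | 0.399 | 0.917 | 2.75 | about 77% |
| 0.7 | 0.239 | 0.737 | 2.05 | about 51–52% |

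Simulation under the same assumptions gives 91%, 77% and 52%. The nominal rate in the direction of improvement is 2.5%. Stricter entry raises the figures: with a cut-off 1 SD above the mean, the range is 97.5% to 100%.

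**Between-group test, same scenarios.** Both arms drift equally, so the drift cancels. Across cut-offs of 0, 0.5 and 1 SD and correlations of 0.3, 0.5 and 0.7, the two-sample t test on the change rejects in 4.5% to 5.5% of trials.

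**Precision of the randomised contrast.** At a 50% rate with 40 per group, the 95% half-width of the difference is 1.96 × √(2 × 0.25/40) = 0.219, or about ±22 points. At 80% power and two-sided 0.05, the detectable difference is 27 to 31 points for control rates from 22% to 60% (for example 50% against about 80%). Power for 50% against 70% is 45%.

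**The case against.** The strongest reply is that the randomised comparison is already planned in several places, that the named tests (ANOVA, Kruskal–Wallis, chi-square) include methods for independent groups, and that ranking the contrasts is often left to an analysis plan, which is not shown here. It is true that the comparison is planned, and a reader who inferred that the randomisation goes unused would be wrong. But the protocol does not stay silent on the route. It states one, ties it to GDPSF's effect, and mislabels it; an analysis plan would have to overrule that text.

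Two stronger readings are tempting and unsupported. One is that GDPSF will be tested against the 22% to 81% range. Those rates appear only as background, no passage compares results with them, and the sentence names no treatment. It may describe GDPSF itself, in which case it is no control rate. The other is that the analysis cannot be failed. Section 3.1 includes a no-effect level, any fixed benchmark can be missed, and without drift the paired test keeps its nominal error rate.

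It is also fair to say that the simulation does not measure this trial's error rate. The eligibility table is not shown, and the remission outcome has four ordered levels, not a continuous score. The figures illustrate the mechanism.

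The pilot label tempers what is needed but does not remove the defect, because section 2.1 still sets an efficacy objective.

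**Conclusion.** The point holds in this form: the protocol assigns GDPSF's symptom-easing effect to an uncontrolled within-group change under the wrong name, and no passage makes the randomised contrast decide the primary objective. Under the stated assumptions, false improvement appears in about 51% to 91% of trials with no drug effect, against about 5% for the between-group test. The exact size is unknown because the entry cut-off and the correlation are not given. The direction depends only on patients tending to enter when their disease is more active than usual.

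The between-group figure assumes sound random allocation. It also does not mean that the contrast settles everything: with no placebo-only arm and about ±22 points of precision, a non-significant difference from thalidomide would not show equal effect. The protocol makes no such claim; the caution belongs with the contrast once it becomes primary.

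**What to change.** In sections 4.1.1, 4.2 and 5, and in the matching sentence of the abstract:

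- Name GDPSF versus thalidomide at end of treatment as the primary contrast and integrative versus thalidomide as secondary, each reported as a difference with its 95% CI.
- Label within-group before-after change as descriptive and delete historical control as a basis for efficacy.
- State that 40 completers per group give a 95% CI of about ±22 points for a difference in rates near 50%, so the pilot estimates the difference and a non-significant result does not show equal effect. If a superiority or non-inferiority claim is intended instead, say which and, for non-inferiority, state the margin.
- Keep the published rates as background, name the treatment behind the 22% to 81% range, and say that neither range is a benchmark.

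The arms and data are already planned, so the cost is wording only, best settled before analysis. The downside is more modest conclusions.

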### Study design

2.2

This is a single center, double-blinded, randomized, and controlled, parallel-group study. Figure 1 depicts a flow chart of the study. Patients enrolled in this study will randomly be assigned into 3 different groups with respective treatment. Clinical manifestations, blood inflammatory index including erythrocyte sedimentation rate (ESR), C-reactive protein (CRP), and some of the blood biochemical tests will be checked before treatments started (baseline) and will be reexamined on week 4, 8, 12, 18, 20, and 24 during 6 months of treatment to assess the effectiveness and safety. Try to follow up every participant in another 12 months to compare satisfactory rate, complete and partial remission rate, and ineffective rate in different treatment groups.

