### Primary outcome measures

3.1

As the oral and genital ulceration, skin lesions (erythema nodosum) are most common complaints in BD patients. We select a mucocutaneous activity index (MAI) in BD created by Mumcu et al.^[14]^ In this MAI:Presence of the lesion was coded as 1 for actives and 0 for inactives (0 vs 1 point)Pain was evaluated by 100 mm-visual analogue scale (VAS; 0: no pain–100: severe pain) by patients. Then, the VAS score was categorized to calculate the score as follows: ≤10: 0; 11–20: 1; 21–40: 2; 41–60: 3; 61–80: 4; 81 and over: 5 points.Functional status was evaluated by a 5-point Likert-type scale: none of the time (0 points), little of the time: 1 point, some of the time: 2 points, most of the time: 3 points and all of the time: 4 points. Mean score was used in the index (Table 2).

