**Figure 3 F3:**
[figure not shown]
Schedule of enrollment, interventions, and assessments (using the SPIRIT 2013 statement). AE = adverse event, BD-QoL = quality of life for Behcet disease, CRP = C-reactive protein, ESR = erythrocyte sedimentation rate, GDPSF = Glycyrrhizae Decoction for Purging Stomach-Fire, GGT = gamma-glutamyl transpeptidase, Ig = immunoglobulin, MAI = mucocutaneous activity index.

IBM SPSS 21 Statistics will be applied for the analysis. Measurement data that followed normal distribution will be recorded as mean ± SD and analyzed by ANOVA or *t* test, otherwise, Kruskal–Wallis will be applied. Count data will be analyzed by χ^2^ test. The statistical significance level was set at *P* < .05 for all the tests.

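### The MAI is read at five or six on-treatment visits, but the analysis text names no method that uses the repeated readings; a baseline-adjusted mean over weeks 12 to 24 would probably be more precise

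*Protocol article*

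**What the plan says.** The article's Primary outcome measures (3.1) state "We select a mucocutaneous activity index (MAI) in BD". The index combines a 0/1 item for lesion activity, a categorised pain score and a functional-status score. The Discussion describes the condition as relapsing: "The symptoms caused by the disease especially recurrent oral and genital ulceration cause pain".

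Study design (2.2) has clinical manifestations checked at baseline and says they "will be reexamined on week 4, 8, 12, 18, 20, and 24 during 6 months of treatment to assess the effectiveness and safety". That is six on-treatment assessments. Statistical analysis (4.2) says instead that "participants will visit investigators every 4 weeks 5 times in all", and then: "Their clinical manifestations (MAI), blood tests, thalidomide dosage in thalidomide, and integrative groups will be assessed". So the MAI is read repeatedly on treatment, but the two sections disagree on how often and when.

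On the comparison itself, section 4.2 says "The data of assessments on each intervention group before and after treatments will be collected and analyzed" by what it calls historical control, and that groups are compared by intergroup control. After the Figure 3 legend it lists ANOVA or t test for normally distributed measurements ("otherwise, Kruskal–Wallis will be applied") and the chi-square test for counts. It does not say which on-treatment MAI reading, or which summary of the readings, is compared.

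**The concern.** In a recurrent disease, one post-treatment reading reflects both a patient's general level of disease and where that patient happens to be between flares. Averaging several readings reduces the second component at no extra cost, because the visits are already scheduled. The article's analysis section describes a before/after contrast and lists tests that, in their ordinary form, take one value per patient. Followed as written, it would leave most on-treatment MAI readings out of the treatment comparison. If the choice of reading is merely left open, several candidate values exist and the text does not prevent the choice being made after the results are seen. With about 40 evaluable patients per group, the choice of summary visibly changes the chance of detecting a moderate difference.

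**Working it through.** **Inputs from the article.** 50 patients per group and 20% dropout (Sample size calculation, 4.1.1); significance level 0.05 (4.2); visits at weeks 12, 18, 20 and 24 within the later treatment period (2.2). The sample size section gives no power, effect size, SD or correlation, so 150 cannot be re-derived. It is only arithmetically consistent: 3 × 50 = 150, and 50 × 0.80 = 40 evaluable per group.

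**Assumptions.** Two-sided test; one pairwise comparison of two groups of 40; difference of 0.5 single-visit SD at week 24; the same correlation ρ between any two readings, baseline included, with ρ = 0.3 to 0.5. Power is from the noncentral t distribution.

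**Step 1: variance of a mean of k visits relative to one visit,** V = (1 + (k − 1)ρ)/k.
- k = 4: (1 + 0.9)/4 = 0.475 at ρ = 0.3; (1 + 1.5)/4 = 0.625 at ρ = 0.5.
- k = 6: (1 + 1.5)/6 = 0.417; (1 + 2.5)/6 = 0.583.

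**Step 2: equal effect at every visit, no baseline adjustment.**
- One reading: standardised difference 0.5, power 59.8%.
- Mean of weeks 12–24: 0.5/√0.475 = 0.725, power 89.3%; 0.5/√0.625 = 0.632, power 79.8%.
- Difference detectable with 80% power: 0.634 SD for one reading; 0.634 × √0.475 = 0.437 SD and 0.634 × √0.625 = 0.501 SD for the mean of four.

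**Step 3: effect growing linearly to week 24, no baseline adjustment.**
- Average share of the week-24 effect: (12 + 18 + 20 + 24)/(4 × 24) = 0.771 for the four later visits; (4 + 8 + 12 + 18 + 20 + 24)/(6 × 24) = 0.597 for all six.
- Mean of weeks 12–24: 0.5 × 0.771 = 0.385. Divided by √0.475 and √0.625 this gives 0.559 and 0.488, power 69.5% and 57.7%.
- Mean of all six: 0.5 × 0.597 = 0.299. Divided by √0.417 and √0.583 this gives 0.463 and 0.391, power 53% and 41%.
- Week 24 alone stays at 59.8%, so the all-visit mean loses power here. The later-visit mean gains at ρ = 0.3 and falls slightly short at ρ = 0.5.

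**Step 4: adjusting for baseline MAI.** The residual variance is V − ρ².
- Week 24: 1 − 0.09 = 0.91; 1 − 0.25 = 0.75.
- Mean of weeks 12–24: 0.475 − 0.09 = 0.385; 0.625 − 0.25 = 0.375.
- Linear build-up, mean of four: 0.385/√0.385 = 0.621 and 0.385/√0.375 = 0.629.
- Week 24: 0.5/√0.91 = 0.524 and 0.5/√0.75 = 0.577.

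| Power | ρ = 0.3 | ρ = 0.5 |
|---|---|---|
| Week 24, unadjusted | 59.8% | 59.8% |
| Weeks 12–24 mean, unadjusted, equal effect | 89.3% | 79.8% |
| Weeks 12–24 mean, unadjusted, linear build-up | 69.5% | 57.7% |
| Week 24, baseline-adjusted | 64% | 72% |
| Weeks 12–24 mean, baseline-adjusted, linear build-up | 78% | 79% |

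At ρ = 0.7 with linear build-up, the adjusted comparison is 89% for the mean against 87% for week 24.

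**Visit count.** The four later visits come from the list in 2.2. Five visits four weeks apart, starting at week 4, would end at week 20 and leave only weeks 12, 16 and 20 in the window. The exact gain therefore depends on which schedule is correct.

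**The case against.** The strongest reply is that the article never says that one reading is used. ANOVA can include repeated measures, and a t test can be run on a visit mean. The before/after wording is attached to the within-group analysis; for the comparison between groups the article says little more than that it will be made. This stands. A reader might infer that the plan commits to the week-24 value and discards the rest, but no sentence says so or names that visit. What remains is narrower: the section describes a contrast and lists tests, and nothing in it brings the repeated readings into the treatment comparison.

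A reader might also infer that the MAI is a same-day snapshot, so that a patient could score zero after weeks of ulcers. The article does not settle this. The functional items are graded by how much of the time, which suggests a recall period, and the table defining the index is not available. A much larger penalty could be obtained by assuming short ulcer episodes and a very low between-visit correlation, but neither figure is in the article.

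The primary section also grades remission using relapse frequency, which draws on more than one time point. That is a separate four-level outcome and does not bring the intermediate MAI scores into the MAI comparison. Still, together with the description of the trial as a pilot that makes no power claim, it means the MAI summary cannot be said to decide the trial.

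Finally, averaging helps only if the effect is present at the visits averaged. This objection is sound against a mean over all visits (Step 3). The integrative group's flexible thalidomide dose is a further reason not to presume an equal effect at each visit. Restricting the mean to weeks 12–24 and adjusting for baseline largely answers it: that version was ahead of the adjusted week-24 value in each case worked above.

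**Conclusion.** The point holds in moderate form. The primary measure is read repeatedly in a recurrent disease, and the stated analysis names no way of using those readings. If one post-treatment value is what is meant, precision from visits already scheduled is given up. Under the stated assumptions, unadjusted power of 60% compares with about 80%–89% for the later-visit mean under an equal effect. With linear build-up, the baseline-adjusted mean keeps an advantage of about 14 points at ρ = 0.3 (78% against 64%) and 7 points at ρ = 0.5 (79% against 72%). The sizes depend on a correlation, an effect size and a time course that the article does not supply. The disagreement over five or six visits is a plain inconsistency whatever summary is chosen.

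**What to change.** First, reconcile the visit schedule in Study design (2.2) with that in Statistical analysis (4.2), and state at which visits the MAI is scored.

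Then add one sentence to section 4.2: the between-group MAI analysis compares each patient's mean MAI over the scheduled visits from week 12 to week 24, adjusted for baseline MAI; the week-24 value and the remission grade are reported alongside. A mean over all on-treatment visits should not be the default, because it can lose power if the effect builds slowly.

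The cost is wording only, with no new visits, data or patients. The small downside is a change in what is measured: disease burden over later treatment instead of status at week 24. Reporting the week-24 value alongside keeps that information available.
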